# Macrophage Therapy for Acute Liver Injury (MAIL): a study protocol for a phase 1 randomised, open-label, dose-escalation study to evaluate safety, tolerability and activity of allogeneic alternatively activated macrophages in patients with paracetamol-induced acute liver injury in the UK

**DOI:** 10.1136/bmjopen-2024-089417

**Published:** 2024-12-09

**Keywords:** Hepatology, Toxicology, Clinical Trial

## Abstract

**Introduction:**

Acute liver failure (ALF) has no effective treatment other than liver transplantation and is commonly caused by paracetamol overdose. New treatments are needed to treat and prevent ALF. Alternatively-activated macrophages (AAMs) can promote resolution of liver necrosis and stimulate hepatocyte proliferation. Using AAMs in unscheduled care requires the use of an allogeneic product. A clinical trial is needed to determine the safety and tolerability of allogeneic AAMs.

**Methods and analysis:**

A single-centre, open-label, dose-escalation, phase 1 randomised trial to determine whether there is dose-limiting toxicity of AAMs in patients with paracetamol-induced acute liver injury. Randomisation will occur at higher doses. Between 17 and 30 patients will receive treatment, subject to dose-limiting toxicity and an adaptive trial design which aims to reduce the risk of allocation bias through blinding and randomisation.

**Ethics and dissemination:**

The trial will be conducted according to the ethical principles of the Declaration of Helsinki 2013 and has been approved by North East—York Research Ethics Committee (reference 23/NE/0019), National Health Service Lothian Research and Development department, and the UK Medicines and Healthcare products Regulatory Agency. When the trial concludes, results will be shared by presentation and publication.

**Trial registration number:**

ISRCTN12637839.

STRENGTHS AND LIMITATIONS OF THIS STUDYThis phase 1 study uses randomisation with concealed allocation to reduce the risk of allocation bias.The study will use a variety of biomarkers and clinical assessment to identify the safety and tolerability of allogeneic macrophages in humans with acute liver injury.This study has the potential to lay the foundation for a phase 2 clinical trial of an ‘off-the-shelf’ macrophage product for acute liver injury.

## Introduction

### Background

 Acute liver failure (ALF) has no effective treatment other than liver transplantation, which has associated morbidity/mortality, expense and a scarcity of donor livers.^1^ The most common cause of ALF is paracetamol (acetaminophen) overdose (POD). In the UK, around 50 000 people need emergency treatment with acetylcysteine (n-acetylcysteine, NAC), every year.^2^ The USA has around 89 000 hospital visits annually for POD, with an estimated annual treatment cost of US$1 billion.^3^ Around 10% of these patients develop biochemical evidence of acute liver injury (ALI) and around 1 in 200 develop ALI severe enough after POD to need a liver transplant.^4^ Mortality in the ALF group is around 30%–35%, with about 30% receiving a liver transplant (most of whom survive but will require lifelong ongoing treatment and often have morbidity secondary to the immunosuppression required for transplantation).^1^ Many of these patients occupy critical care beds for weeks. Aside from paracetamol, there is a wide range of other causes for ALF including non-paracetamol drug-induced liver injury and viral infection. There is no specific treatment for ALF due to non-paracetamol causes (NAC is sometimes used but has modest efficacy).^5^

In cases of POD, the metabolic pathways that eliminate the drug become saturated and a highly reactive metabolite, N-acetyl-p-benzoquinone imine (NAPQI), is made in excess by the cytochrome P450 enzyme system. NAPQI is directly toxic to hepatocytes and leads to liver necrosis.^6^ The immune system responds by a massive infiltration of circulating inflammatory monocytes into the liver.^7^ These cells create a highly toxic inflammatory environment. In humans, the degree of infiltration of monocytes, identified by concurrent monocytopenia in the circulation, reflects the degree of ALI.^8^ Over a period of 24–48 hours, liver-infiltrating monocytes differentiate to macrophages which adopt an anti-inflammatory, wound-healing phenotype (‘M2’).^7^ These macrophages initiate the healing process and facilitate the transition from the initial inflammatory phase of ALF to the resolution phase. Macrophage-mediated resolution of ALI comprises phagocytosis of necrotic hepatocytes, induction of regeneration by proliferation of hepatocyte progenitors and suppression of systemic inflammation via an anti-inflammatory cytokine effect.^9^

Currently, the only effective treatment for preventing ALI after POD is NAC. If treatment is commenced within 8 hours of overdose, then NAC is nearly 100% effective. However, effectiveness drops substantially when treatment is delayed; NAC is nearly ineffective when treatment is delayed greater than 20 hours after overdose, though delayed treatment may reduce the subsequent development of hepatic encephalopathy and mortality.^10 11^ There is a clear unmet need for new treatments to prevent and/or treat ALF.

### Rationale for study

We urgently need a treatment which prevents the progression of ALI to ALF to prevent liver transplantation or death. Halting or reversing progression to ALF would be life-saving and remove the need for immunosuppression and morbidity/mortality associated with transplantation. The proposed solution is to develop allogeneic alternatively-activated macrophages (AAMs) as a treatment.^12^ An allogeneic product is necessary for the acute setting, when autologous monocytes may have altered properties, and there is insufficient time to produce autologous cell products.^13^ This cell therapy has clear efficacy when delivered after liver injury is established in mouse models.^14^ This is because macrophage therapy reverses injury rather than preventing it. Early phase human studies of chronic liver disease using autologous macrophage therapy have provided evidence to support the safety of AAMs, but a phase 1 trial is required to establish whether an allogeneic product is feasible.^15^

The primary aim of this trial is to determine the safety and tolerability of AAMs. There are multiple causes of ALF other than paracetamol, but POD is the most common cause in the UK and patients typically have a clearly defined onset of injury and blood tests to confirm the diagnosis. Due to the distribution and mechanisms of action of AAMs, healthy volunteers are not a suitable test population. AAMs localise to injured liver tissue, where they target necrotic hepatocytes and reduce inflammatory factors. Therefore, humans with healthy livers would not provide meaningful safety or activity data.

If successful, this study will pave the way for a randomised controlled trial of the effectiveness of macrophage cell therapy in patients with paracetamol-induced ALI and facilitate the development of macrophage cell therapy for other causes of ALF. Here, we summarise the MAIL (Macrophage therapy for Acute Injury to the Liver) trial protocol in accordance with the Standard Protocol Items: Recommendations for Interventional Trials (SPIRIT) guidance for randomised trial protocols and the SPIRIT-DEFINE extension for dose-finding studies.^16^

### Objectives

The primary objective of this phase 1 trial is to determine whether there is dose-limiting toxicity (DLT) produced by allogeneic AAMs in patients with paracetamol-induced ALI.

The secondary objectives are to explore the safety, activity and immunogenicity of allogeneic AAMs in patients with paracetamol-induced ALI.

### Trial design

MAIL is a single-centre, open-label, dose-escalation, phase 1 randomised trial to determine whether there is DLT of AAMs in patients with paracetamol-induced ALI. Randomisation will occur at higher doses. Sentinel dosing of patients and dose escalation decisions will be guided by an independent Data Monitoring Committee (DMC).

Figure 1A describes the planned trial design. The heterogeneity in patient outcomes following the development of paracetamol-induced ALI leads to a risk of allocation bias if the next dose of cells to be given is known by the recruiting team, as less unwell patients could be preferentially enrolled at higher doses. Therefore, we will use randomisation with concealed allocation at higher dosing levels and will blind the recruiting team to prevent prediction of the next dose of AAM treatment.

**Figure 1 F1:**
[figure not shown]
(A) Overview of MAIL trial design—scenario 1 (rapid escalation). In cohort 1, the first patient will be dosed with 106 cells. In scenario 1, there is no safety concern following DMC review and the dose is escalated to 107 (cohort 2) and then into randomised blocks in cohorts 3, 4 and 5. A green arrow represents a DMC recommendation to dose escalate. A red arrow indicates a DMC recommendation to expand at that dose. The blue arrow indicates a trial team option to expand at the highest dose. Yellow squares are sentinel dosed patients. The highest dose is up to 10^9^ cells. (B) Overview of MAIL trial design—scenario 2. In scenario 2, there is a safety signal in cohort 2 and the DMC advise two further patients are added. No further signals are observed at 107 and the 107 doses are dropped from the randomisation in cohorts 3 and 4. A green arrow represents a DMC recommendation to dose escalate. A red arrow indicates a DMC recommendation to expand at that dose. The blue arrow indicates a trial team option to expand at highest dose. Yellow squares are sentinel dosed patients. The highest dose is up to 10^9^ cells. (C) Overview of MAIL trial design—scenario 3 (3+3 escalation). In scenario 3, there is a safety concern and there is expansion of cohorts 1 and 2 into 3+3 blocks. Each square represents one patient dosed at the dose indicated, except the +3 box which indicates an option to dose three further patients at the highest dose in that cohort. A green arrow represents a DMC recommendation to dose escalate. A red arrow indicates a DMC recommendation to expand at that dose. Yellow squares are sentinel dosed patients. The highest dose is up to 10^9^ cells. DLT, dose-limiting toxicity; DMC, data monitoring committee; MAIL, Macrophage therapy for Acute Injury to the Liver.

Extrapolating from mouse models, we predict the clinically active dose will be between 10^8^ and 10^9^ cells. The biologically active dose in mouse models of paracetamol liver injury is 10^6^ cells (the lowest trial dose). Scaling up to humans, the predicted human equivalent dose is between 2×10^8^ (if calculated using body surface area) to 2×10^9^ (using body weight). If allometric scaling is used with liver weight and blood flow as variables the human equivalent dose of AAMs is around 10^9^ (the highest trial dose).

Within each dosing cohort, the first participant to receive the highest dose will be a sentinel dosing patient. There will be at least 1-week pause to recruitment following the conclusion of each dosing cohort. The DMC will make a decision on dose progression using data which will include all unblinded demographic, concomitant medications, infusion, physiological, safety and activity data gathered at days −1, 0, 1, 2 (if applicable) and 7 at a minimum, which will be quality-control checked before DMC review. Data from day 30 will also be included if available at the time of the DMC meeting. The sponsor, chief investigator and trial steering committee (TSC) will review the DMC recommendation and make a documented decision regarding dose progression.

For all dosing cohorts, the DMC can recommend a further three patients be dosed at the highest dose in that cohort. If one participant in a dose cohort experiences potential DLT, then the DMC can recommend treating three additional participants at the same dose. If DLT occurs in two or more patients in any size of dose cohort, then recruitment should end.

If there is a safety signal in dose cohorts 1 or 2, the DMC can recommend the addition of two extra patients to that cohort. If a further two patients are recommended by the DMC in cohort 2 (10^7^) but not in cohort 1 (10^6^) and no further signals are observed at 10^7^ (scenario 2—figure 1B), then the 10^7^ doses are dropped from the randomisation in cohorts 3 and 4 (four patients randomised: three at higher dose and one at 10^6^).

If an additional two patients are recommended by the DMC in cohort 1 (10^6^), then two patients must also be added to cohort 2 (10^7^). The trial design would thereafter effectively follow a ‘3+3’ phase 1 trial design (scenario 3—figure 1C).^17^

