### Interventions

The product under investigation is an allogeneic, AAM cell therapy given via peripheral venous infusion at doses from 10^6^ up to 10^9^. The AAM product will be manufactured by the Scottish National Blood Transfusion Service using healthy volunteer donations at a licensed site using methodology described previously, with the addition of an optimised cryopreservation step. This allows for rapid deployment of the AAM product with good macrophage viability.^18 19^ The product has received manufacturing approval from the MHRA. The duration and rates of AAM infusion are given in table 1.

**Table 1 T1:** Duration and rate of intravenous AAM infusion by dose cohort

Dose cohort	Maximum dose (cell number)	Minimum duration (minutes)	Maximum rate (cells per minute)
1	1×10^6^	5	2×10^5^
2	1×10^7^	5	2×10^6^
3	1×10^8^	5	2×10^7^
4	3×10^8^	10	3×10^7^
5	1×10^9^	30	3×10^7^

AAMsalternatively activated macrophages

In addition to AAMs, all patients will be treated with acetylcysteine per standard clinical care. The SNAP regimen for delivering acetylcysteine will be used as recommended by the National Poisons Information Service via TOXBASE (www.toxbase.org) and endorsed as the default standard of care by the Royal College of Emergency Medicine.^20^ The SNAP regimen has a substantially lower rate of adverse drug reactions, which will facilitate the identification of treatment-emergent adverse events due to the cell therapy.

Chlorphenamine 10 mg will be administered intravenously approximately 30 min ahead of macrophage infusion to minimise the likelihood of allergic reaction. If a patient has known allergies or contraindications to chlorphenamine, 10 mg cetirizine hydrochloride will be taken orally instead.

The time interval between overdose and AAM treatment is not defined. Patients in both the progression phase of injury and recovery phase may receive AAMs.

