### Outcomes

#### Primary outcome

DLT occurs within 30 days of infusion. DLT is defined as a clinically significant adverse event or abnormal laboratory value assessed as unrelated to disease progression, intercurrent illness or concomitant medications and either meeting the National Cancer Institute Common Terminology Criteria for Adverse Events Grade 3, 4 or 5, or deemed by the independent DMC to be serious enough to prevent an increase in dose of treatment.

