#### Randomisation

The dose assigned to the sentinel participant in each cohort will be fixed. For the remainder of cohorts 3, 4 and 5 randomisation, using computer-generated pseudo-random numbers produced by the programming team at Edinburgh Clinical Trials Unit (ECTU), will use the allocation ratios across available doses depicted in figure 1A,B as appropriate.

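### The two-DLT stopping rule counts by numbered cohort, so two DLTs at the same dose in different cohorts force no stop or pause; a pooled-dose pause would close this small gap

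*Protocol article*

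**What the plan says.** All references are to the protocol article.

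- **Binding count (Trial design).** "If DLT occurs in two or more patients in any size of dose cohort, then recruitment should end". The sentence before it is permissive: after one potential DLT in a dose cohort, the DMC may recommend three more patients at that dose.
- **Meaning of dose cohort.** Table 1 (Interventions), titled "Duration and rate of intravenous AAM infusion by dose cohort", numbers the dose cohorts 1 to 5 and gives each a maximum dose. The Blinding section also uses the term for these numbered stages.
- **Mixed doses.** The sentinel's dose is fixed. "For the remainder of cohorts 3, 4 and 5 randomisation" is used across the available doses (Randomisation).
- **Recurring doses.** In scenario 2 the 10^7 "doses are dropped from the randomisation in cohorts 3 and 4", which leaves "four patients randomised: three at higher dose and one at" 10^6. So in scenario 1 both 10^6 and 10^7 sit in cohorts 3 and 4.
- **Timing.** "There will be at least 1-week pause to recruitment following the conclusion of each dosing cohort". The DMC needs data to day 7 at least; "Data from day 30 will also be included if available at the time of the DMC meeting". The primary outcome has a longer window: "DLT occurs within 30 days of infusion".
- **Other pauses (Monitoring and oversight).** Enrolment halts for death or escalation to critical care or the transplant unit, for an event of particular interest, or for a suspected unexpected serious adverse reaction. No DLT count is listed.

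**The concern.** Two DLTs at one dose are the evidence that a dose-limiting rule is meant to catch. Once cohorts mix doses, the binding rule counts something else. It ends recruitment for two DLTs at different doses in one cohort, but not for two DLTs at the same dose in two cohorts.

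Take one DLT at 10^7 in cohort 3, one at 10^7 in cohort 4, and none elsewhere. With the cohort 2 patient, that is 2 of 3 patients at 10^7. If neither event is on the pause list, dosing in cohort 4 may continue, including at 3×10^8, with no required DMC review first. A grade 3 laboratory value can be a DLT (Primary outcome) without being on the list.

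The issue is current. Study amendments and current status reports scenario 1, with the first participant in cohort 3, the first mixed cohort, recruited.

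**Working it through.** **Layout.** Figure 1 is not shown, so the layout is inferred. The one figure to reproduce is the scenario 1 total of 17 (Sample size and statistical analysis). The article gives no operating characteristics for the stopping rule.

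- Layout A: cohorts of 1, 1, 5, 5, 5 = 17. Cohorts 3 and 4 each hold three at the top dose, one at 10^7 and one at 10^6. Cohort 5 holds three at 10^9 and two lower-dose patients.
- Layout B: if the four randomised patients of scenario 2 come on top of the sentinel, cohorts 3 and 4 in scenario 1 hold 4 + 1 + 1 = 6, and 1 + 1 + 6 + 6 + 3 = 17. Cohort 5 is taken as two at 10^9 and one lower. Two patients at 10^9 fit the article's 3–4 per group less well, so this layout serves as a sensitivity case.

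**Assumptions.** DLTs are independent, with risk p per patient and q = 1 − p. There is no DLT in cohorts 1 and 2, and no DLT is on the pause list. The last makes the results upper bounds.

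**Step 1: two DLTs at 10^6 or 10^7 by the end of cohort 4, rule silent.** Each of cohorts 3 and 4 must have exactly one DLT, both at 10^6 or both at 10^7. The other 8 (A) or 10 (B) patients have none. P = 2p²q^8 (A) or 2p²q^10 (B).

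| p | A | B |
|---|---|---|
| 5% | 2 × 0.0025 × 0.6634 = 0.33% | 2 × 0.0025 × 0.5987 = 0.30% |
| 10% | 2 × 0.01 × 0.4305 = 0.86% | 2 × 0.01 × 0.3487 = 0.70% |
| 20% | 2 × 0.04 × 0.1678 = 1.34% | 2 × 0.04 × 0.1074 = 0.86% |

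The formula for A peaks at p = 2/10, so 1.34% is its maximum over any common risk. Cohort 5 plays no part.

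With illustrative rising risks of 1, 2, 5, 10 and 20% from 10^6 to 10^9, A gives (0.01² × 0.98² + 0.02² × 0.99²) × 0.95³ × 0.90³ = 0.000488 × 0.625 = 0.03%.

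If the DMC always adds three patients at the affected dose after the cohort 3 DLT, and they have none, multiply A by q³: 0.28%, 0.63% and 0.69%.

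**Step 2: any dose, whole trial, p = 10%.** Each of cohorts 3–5 has at most one DLT, and two share a dose. With M such pairs and T such triples (one patient per cohort), P = M p²q^13 + T p³q^12, where q^13 = 0.2542 and q^12 = 0.2824.

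- A, cohort 5 lower doses 10^8 and 3×10^8: M = 8, T = 40; 0.0203 + 0.0113 = 3.2%.
- A, lower doses 10^6 and 10^7: M = 6, T = 26; 0.0153 + 0.0073 = 2.3%.
- B, lower dose 10^8: M = 6, T = 30; 0.0153 + 0.0085 = 2.4%.
- B, lower dose 10^6: M = 4, T = 16; 0.0102 + 0.0045 = 1.5%.

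The range is 1.5–3.2% over the layouts tried.

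**Step 3: who is still to be dosed.** Suppose the second DLT is in a lower-dose patient of cohort 4. In A, two non-sentinel 3×10^8 patients are in random order with that patient, so at least one follows with probability 1 − 1/3 = 2/3 (mean 2 × 1/2 = 1). In B there are three: 1 − 1/4 = 3/4 (mean 1.5).

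**Step 4: cost of a pooled-dose pause (A).** The cohort rule alone fires in cohorts 3–5 with probability 1 − (q^5 + 5pq^4)³: 6.6%, 22.5% and 59.9% at p = 5, 10 and 20%. Adding the pooled pause gives 7.6–7.9%, 24.8–25.7% and 62.7–63.9%, which is 1.0 to 4.0 points more.

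**The case against.** **Existing safeguards.** A reader might infer that no numeric rule acts at all in the example. The article does not support that. The one-DLT provision has a threshold of one, is tied to the dose, and applies in both cohorts. It is optional, however, and neither pauses dosing nor adds up DLTs across cohorts. Unblinded DMC review also precedes every escalation, and the DMC can stop the study (Data monitoring). What remains is the time within a cohort and late DLTs.

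**Many DLTs already pause enrolment.** A DLT is by definition not put down to disease progression, intercurrent illness or other medication, so a serious and unexpected one would usually be on the list. The transfusion-reaction criteria in Table 4 are broad, and a DMC-judged DLT already involves the DMC. This stands, and is why the figures are upper bounds.

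**Should the trial end in the example?** A reader might infer that it should. That does not follow. If the rule is silent at the end of cohort 4, all six patients at 10^8 and 3×10^8 (eight in layout B) were free of DLT. Pooled from 10^7 upwards, the rate is 2/9 in layout A. A pause suits this evidence better than a mandatory end.

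**Larger probabilities.** Counting cohorts 1 and 2 in layout A gives 2.0%, 5.2% and 7.0% at 5, 10 and 20% risk. Those figures ignore that a signal there can move the trial to scenario 2 or 3, and the article reports scenario 1.

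**Day 7 against day 30.** Seventeen patients over about 24 months is one per 1.4 months, so most day-30 data should exist at each review. The last patients of a cohort are the exception. Pooling does not bring day-30 data into the review; it only makes a late DLT count once known.

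**Charter.** The DMC charter is not shown and may govern single DLTs. The article nevertheless states the binding rule in full, and as stated it counts by cohort.

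**Conclusion.** The point holds as a minor one. The only binding DLT count works by numbered cohort, so two DLTs at 10^6, or in scenario 1 at 10^7, split between cohorts 3 and 4 force neither a stop nor a pause unless an event is on the enrolment-pause list. The exposed case is mainly a second, unlisted DLT at the same dose arising mid-cohort, or a late one from an earlier cohort.

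It is rare: at most about 0.3%, 0.7–0.9% and 0.9–1.3% of trials at equal risks of 5, 10 and 20%, and 0.03% under the rising risks. For any dose over the whole trial it is about 1.5–3.2% at 10% risk. The recurrence of doses comes from the text. The cohort sizes, the make-up of cohort 5 and all DLT risks are assumptions. Scenario 3, effectively a 3+3 design, appears to hold one dose per cohort and so seems unaffected.

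**What to change.** Keep the cohort rule, since it also catches two DLTs at different doses within one cohort. Add one sentence after it:

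*Two or more DLTs at the same dose level, pooled over all cohorts, pause enrolment at once, including mid-cohort, for DMC review before any further dosing; the DMC decides whether recruitment ends.*

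This needs a one-sentence amendment and no extra patients. The cost is about 1–4 percentage points more stops or pauses, depending on the DLT risk. The added part is only a pause, so it costs recruitment time and leaves the decision with the DMC.
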